#### Processes

The scoping review will follow PRISMA guidelines and procedures [26, 27]. The literature search will include three steps to (1) identify common methods, (2) search the literature for identified methods based on the first step, and (3) review references from the included papers to identify additional literature. For details on search terms and databases utilized, see Table 1. Articles identified in the literature review will be screened using a title and abstract review. Finally, articles determined to be eligible following the title and abstract review will be evaluated in the full-text review (Table 2).

**Table 1 Tab1:** Scoping review search terms and databases

Search terms/description	Databases
(“implementation strategy” or “implementation strategies”) AND (“child” OR “pediatric” OR “children”) AND (“mental health service” OR “evidence-based practice” OR “evidence based intervention” or “mental health treatment”)	PsycInfo
	Social Services Abstracts
	PubMed
(“concept mapping” OR “conjoint analysis” OR “group model building” OR “intervention mapping”) AND (“implementation strategy” OR “implementation strategies”) AND (“child” OR “pediatric” OR children) AND (“mental health service” OR “evidence-based practice” OR “evidence based intervention” or “mental health treatment”)	PsycInfo
	Social Services Abstracts
	PubMed
Review references in papers identified via searches 1 and 2 to identify additional relevant literature	N/A

**Table 2 Tab2:** Scoping review eligibility criteria

Inclusion criteria	Exclusion criteria
Title and abstract review	
- Discusses selecting/tailoring/mapping implementation strategies to address implementation determinants - Describes a method for selecting/tailoring/ mapping implementation strategies - Providers work with child populations (< 18) - Implementing mental health practices/interventions	- Article not in English - Providers who work exclusively with adult populations (> 18 years) [If providers work with a range (e.g., 16–25) that includes individuals under 18 years old, *include*] - Non mental-health practices/interventions
Full-text review	

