- Includes description of a strategy/method (e.g., concept mapping, intervention mapping) for tailoring implementation strategies to identified determinant - Delivery of MH-EBPs to child populations	- Article not in English Sample details: - Providers who work exclusively with adult populations (18 +) [If providers work with a range (e.g., 16–25) that includes individuals under 18 years old, *include*] - Non mental-health practices/interventions - Article does not provide information on the population of focus ISMM details: - Article does not mention selecting/tailoring/mapping implementation strategies - Article does not describe the method for selecting/tailoring/mapping implementation strategies

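### Table 2 tests for a described mapping method at title/abstract review, so papers that set out their method only in the body risk exclusion unread

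*Protocol article*

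**What the plan says.** All of this is in the Protocol article, Aim 1, Processes, including Table 2.

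- **Title/abstract inclusion.** There are four criteria. Two concern the mapping content and are listed separately: "Discusses selecting/tailoring/mapping implementation strategies to address implementation determinants" and "Describes a method for selecting/tailoring/ mapping implementation strategies". The other two are a child population and a mental-health practice.
- **Title/abstract exclusion.** There are three reasons: not in English, providers who see only adults, and practices outside mental health. None concerns the mapping method.
- **Passage to the next stage.** The text states that "articles determined to be eligible following the title and abstract review will be evaluated in the full-text review".
- **Full-text inclusion.** The method criterion is "Includes description of a strategy/method (e.g., concept mapping, intervention mapping) for tailoring implementation strategies to identified determinant", alongside delivery of mental-health practices to children.
- **Full-text exclusion.** The three title/abstract reasons are repeated. Added to them are a lack of population information, "Article does not mention selecting/tailoring/mapping implementation strategies" and "Article does not describe the method for selecting/tailoring/mapping implementation strategies".
- **Supplementary search.** The third search step is to "review references from the included papers to identify additional literature". Table 1 words this more broadly, as the references of papers identified by the first two searches.

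**The concern.** Whether a paper describes how strategies were matched to determinants can usually be settled only by reading its methods section. Abstracts are short, and a study that used mapping as one step of a larger implementation project may say only that strategies were tailored to barriers. A first-stage criterion that asks for a described method therefore screens on how the abstract was written as well as on what the study did.

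The Aim 1 Analyses plan counts how often each method is used, describes the methods by content analysis, and gathers data on rigor and feasibility. All three draw on the included papers. If papers built around a named method pass more easily than papers that applied one in passing, the error has a direction. The section on considerations and limitations already expects a thin literature and accepts that the eligibility criteria may shrink it, so avoidable exclusions carry more weight.

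**Working it through.** The plan gives no figure on this point and no arithmetic reproduces one. The check sets the columns of Table 2 side by side and follows one record through them.

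**1. The columns**

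| Test | Title/abstract: include | Title/abstract: exclude | Full text: include | Full text: exclude |
|---|---|---|---|---|
| Discusses or mentions selecting, tailoring or mapping | yes | no | within the method criterion | yes |
| Describes the method | yes | **no** | yes | yes |
| Child population | yes | yes (adult-only) | yes | yes (adult-only; no population information) |
| Mental-health practice | yes | yes | yes | yes |
| English | no | yes | no | yes |

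The two method criteria for inclusion are close but not identical: the full-text one ties the method to an identified determinant and gives examples. The full-text exclusion reason is almost a mirror image of the title/abstract inclusion criterion.

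**2. A test record**

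Take a paper on a child mental-health practice, in English. Its abstract says that strategies were tailored to barriers, and its methods section sets out the mapping procedure.

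- Title/abstract inclusion: topic met, population met, practice met, method not met. That is 3 of 4, so the record is not eligible.
- Title/abstract exclusion: 0 of 3 reasons apply, so the record is not excluded.
- Full text, if it were reached: both inclusion criteria are met and no exclusion reason applies, so the paper is included.

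Two screeners could each follow Table 2 faithfully and disagree. One who works from the inclusion column, as the rule on passing to full text suggests, drops a paper that belongs in the review.

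**3. Can another step recover it?**

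The first search string in Table 1 does not require a named method, so such a paper can be retrieved; the risk arises at screening. The second string, as printed, adds the names of four methods and so does not counter a tilt toward named methods. The reference-list step reaches only papers that others cite, under either of its two wordings. No different screening rule is stated for papers found that way, so they would meet the same criterion again.

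**4. Size and direction**

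Let p be the share of truly eligible papers using a given method whose abstracts do not describe it, and s the share of those that screeners drop. Ignoring recovery through reference lists, the fraction of that method's papers retained is 1 − s·p. For methods A and B, the observed ratio of counts is the true ratio multiplied by (1 − s·p_A)/(1 − s·p_B).

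- If p is the same for both methods, and s is too, the counts shrink but their ratio is unchanged.
- If p is lower for methods that authors tend to name in abstracts, the ratio shifts toward those methods.
- If s = 0, nothing is lost.

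The document gives neither p nor s, so the loss lies anywhere from zero to p and cannot be narrowed from the text.

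**The case against.** The strongest reply is that Table 2 may not intend a strict first screen. The method and topic exclusions, and the one for missing population information, appear only at full text. If every first-stage inclusion item were enforced, few records could reach full text and then fail on those grounds, so the table may assume that unclear records advance. This is plausible but not decisive. The full-text column also repeats all three first-stage exclusions, so redundancy is normal in this table and a reason listed at full text need not have been waived earlier. The conflict between the columns remains on either reading: the first-stage criterion either removes eligible papers or does no work.

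A second reply is that naming a method in the abstract may count as describing it, given the examples in the full-text criterion. That would lessen the problem but would favour named methods all the more.

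A reader might infer three stronger claims that the documents do not support:

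- **That eligible papers will certainly be lost.** Table 2 is ambiguous, so this is a risk.
- **That the Aim 2 choice of ISMM rests on the frequency counts.** Aim 2, Processes, bases it on evidence, feasibility and stakeholder involvement. If no method stands out, the limitations section has study personnel weigh the options and consult experts. Aim 1 informs that choice and does not fix it.
- **That the plan has no rule for unclear abstracts.** The article condenses a fuller review protocol, which may contain such a rule. Its absence here is not part of the point.

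**Conclusion.** The point holds as a risk created by a printed criterion. Table 2 asks at title/abstract review for something that is properly judged at full text, asks for it again there, and gives no matching first-stage exclusion reason. Applied literally, the first screen can remove papers that meet every full-text criterion.

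The likely effect is on the completeness of Aim 1 and, if abstract wording differs by method, on the relative frequencies and the description of ISMMs. For Aim 2 the effect is indirect: less evidence on rigor and feasibility to inform the choice. The size is unknown and could be nil if screeners in practice advance records that are silent on the method. This is worth correcting because the correction is cheap and the literature is expected to be sparse; it does not invalidate the review.

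**What to change.** In Table 2, limit title/abstract inclusion to three criteria: the record discusses selecting, tailoring or mapping implementation strategies; the providers work with children; and the practice is a mental-health one. Remove the described-method criterion from that stage and apply it only at full text, where both the inclusion criterion and the matching exclusion reason already stand. If the full review protocol already handles it this way, aligning the table with it is enough.

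The cost is a wording change in one table and some additional full texts to read. The number of extra papers cannot be given without record counts. No new procedure is needed.

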#### Analyses plan

Data extraction will be completed for all articles included following the full-text review. Data will be examined by (a) evaluating the frequency with which each strategy is utilized, (b) conducting content analyses to describe the methods utilized in the literature, and (c) identifying common outcomes measured. Additional data about the rigor of the evidence overall for each method and feasibility data will be gathered.

### Aim 2: pilot test the use of one ISMM within Michigan CMH agencies providing services to autistic youth whose services are funded by the Michigan Medicaid Autism Benefit

Specifically, aim two will examine whether the ISMM increases organizational readiness to change from pre- to post-ISMM, and will evaluate implementation outcomes of the ISMM for selecting and tailoring implementation strategies, including perceived feasibility, acceptability, appropriateness, and usability.

#### Design

A sequential explanatory (QUAN➔QUAL) mixed methods design (Fig. 1) will be utilized for Aim 2. We will evaluate the feasibility, acceptability, appropriateness, and usability of the ISMM for each participating organization; examine stakeholder perspectives on their organization’s readiness for change; and further explore stakeholder perspectives regarding the ISMM using semi-structured interviews.

**Fig. 1 Fig1:**
[figure not shown]
Study design

#### Setting

Purposeful sampling will be utilized to recruit five community-mental health (CMH) agencies in Michigan. Agencies interested in participating will attend a recruitment meeting with the Principal Investigator to review study details and benefits. Agencies will be eligible if they (a) provide services to children on the autism spectrum who are enrolled in Medicaid benefits, (b) identify a need for implementing Project ImPACT within their agency, and (c) endorse an interest in utilizing systematic implementation strategies to facilitate this process.

#### Participants

We will recruit five directors/agency leaders, supervisors, and direct providers at each of the eligible agencies (expected *N* = 25). Participants will be recruited during the agency recruitment meeting and will be asked to complete an online screening form to determine eligibility, if they are interested in participating. Directors/agency leaders will be eligible if they fulfill the role of director or leading decision-maker regarding interventions provided within their agency. At least 1 director/agency leader will be required to participate. Supervisors and direct providers will be eligible if they provide or oversee staff who provide interventions to autistic children who receive their services via the Michigan Medicaid Autism Benefit. Agency staff will be ineligible if they do not read or speak in English.

#### Materials

Aim 2 materials include quantitative measures (described below), qualitative interviews (described below), the ERIC list of implementation strategies, and MAXQDA qualitative coding software. Additionally, any software associated with the selected ISMM may be utilized (e.g., GroupWisdom software for concept mapping).

#### Quantitative measures

##### Demographic and client survey

A questionnaire will be administered to collect provider and organizational demographics as well as information about the clientele receiving services through the CMH setting prior to the first phase of concept mapping.

##### Needs’ assessment

A strength and needs’ assessment based on the Consolidated Framework for Implementation Research (CFIR; [28]). The CFIR is a commonly used determinant framework that facilitates understanding of an implementation context through the identification of implementation barriers and facilitators. This framework includes five domains: intervention/innovation characteristics, outer setting, inner setting, individual characteristics, and implementation process.

##### Readiness for change

Three measures will be utilized to measure readiness for change prior to, and upon completion of, the ISMM. The Organization Readiness for Implementing Change (ORIC; [29]), Organizational Readiness for Change Assessment (ORCA) context scale [30], and Organizational Readiness for Change (ORC; [31]) will be used to elicit participant perspectives regarding their organization’s motivation and capacity to support and facilitate the use of new interventions, such as Project ImPACT, within their organization.

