#### Analyses plan

##### Quantitative analysis plan

The quantitative data collected from questionnaires will be analyzed in three phases. First, analyses will focus on detecting and correcting potential data errors, describing properties, and evaluating the quality of the data. Descriptive analyses will be completed (i.e., means, frequencies, distributions) to report demographic data. Given the limited sample size, paired sample *t*-tests will be conducted to test for changes in perceptions as reported on the ORCA, ORIC, and ORC between pre-and post-ISMM at each agency. Finally, mean responses to the AIM, IAM, FIM, and ISUS will be aggregated by agency after completing the ISMM process to examine the implementation outcomes associated with the ISMM.

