Additionally, because the goal of Aim 2 is to conduct foundational pilot research on the acceptability, feasibility, appropriateness, and usability of an ISMM, other implementation outcomes, such as adoption, fidelity, costs, and sustainability, will not be evaluated. While important constructs within implementation science, recent guidance suggests the need to conduct feasibility and pilot studies on implementation strategies, such as ISMMs, in order to identify potential revisions to the strategy, refine the research design and procedures for future implementation studies, or test the preliminary effects of the strategy on relevant implementation, service and individual-level outcomes [37, 38]. As stated by Proctor and colleagues [5], “the study of implementation strategies should be approached in a similar fashion as evidence-based interventions, for strategies are in fact a type of intervention” (p. 3). Thus, implementation strategies, in their own right, should be empirically tested prior to broader use to ensure that only evidence-based implementation strategies are being disseminated and utilized in usual care settings [4]. Further, this study will include a small number of CMH agencies in Aim 2 study procedures. As a result, the results of the pilot study may not be generalizable to broader systems, geographical locations, or populations. However, the goals of Aim 2 are to gather feasibility data-related implementation strategy procedures and study methods as well as assess potential implementation strategy effects to the use of ISMM within this common service system for autistic youth (e.g., prioritizing external validity) [5, 37, 39].

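### One readiness question is answered by about 15 five-person t-tests on three unranked instruments; one pre-named measure with one overall estimate would answer it better

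*Protocol article*

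**What the plan says.** The protocol article poses the readiness objective as one question with a direction: "aim two will examine whether the ISMM increases organizational readiness to change from pre- to post-ISMM" (opening of Aim 2).

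Under Readiness for change it states that "Three measures will be utilized to measure readiness for change prior to, and upon completion of, the ISMM". The three are the ORIC, the ORCA context scale and the ORC. They share one stated purpose, and none is named as the lead.

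Under Quantitative analysis plan it states: "Given the limited sample size, paired sample *t*-tests will be conducted", and these are "to test for changes in perceptions as reported on the ORCA, ORIC, and ORC between pre-and post-ISMM at each agency".

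The numbers come from two other sections. Setting says "Purposeful sampling will be utilized to recruit five community-mental health (CMH) agencies in Michigan". Participants says "We will recruit five directors/agency leaders, supervisors, and direct providers at each of the eligible agencies", with an expected total of 25. The Processes section of Aim 2 adds that the measures and the analysis do not depend on which ISMM is chosen, so this structure is presented as settled.

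**The concern.** The question is single, but the stated analysis returns one result per instrument per agency, and nothing in the article says how these combine into an answer. Instruments may disagree within an agency, and agencies may disagree on one instrument. A reader of the results could then take any one significant increase among about 15 as support for the ISMM. If nothing had changed, such a result would still turn up far more often than a single test suggests.

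The opposite error matters as much. Five pairs per test give little chance of detecting a moderate real change, so a set of non-significant results would say little about whether readiness rose. Either way, the planned tests are a weak basis for the readiness conclusion.

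**Working it through.** **Inputs from the article.** Five agencies, five participants in each, three instruments, and paired t-tests at each agency. The one stated design figure reproduces: 5 × 5 = 25.

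**Assumptions, because the article does not state them.** Two-sided 5% tests, so 2.5% in the direction of increase; one total score per instrument; independent agencies; normally distributed changes; a correlation between the instruments' change scores anywhere from 0 to 1. SD means the standard deviation of the within-person pre-post differences.

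**Number of tests.** 3 instruments × 5 agencies = 15, each with five pairs and 4 degrees of freedom. Testing subscales would add more.

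**Chance of at least one false result.** For k independent tests at level a this is 1 − (1 − a)^k. Perfectly correlated instruments reduce the 15 tests to 5.

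- False increase, independent: 1 − 0.975^15 = 31.6%
- False increase, perfectly correlated: 1 − 0.975^5 = 11.9%
- Either direction, independent: 1 − 0.95^15 = 53.7%
- Either direction, perfectly correlated: 1 − 0.95^5 = 22.6%

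Between these ends, 60,000 null trials were simulated (5 agencies × 5 people × 3 equally correlated change scores). The end rows are the exact values above.

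| Correlation between instruments | False increase, two-sided 5% | Either direction, two-sided 5% | False increase, one-sided 5% |
|---|---|---|---|
| 0 | 31.6% | 53.7% | 53.7% |
| 0.5 | 29.1% | 50.6% | 48.3% |
| 0.7 | 26.5% | 47.1% | 44.1% |
| 0.9 | 21.4% | 38.9% | 36.1% |
| 1 | 11.9% | 22.6% | 22.6% |

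For correlations of 0.9 to 0.5 under two-sided testing, the inflation over 2.5% is 21.4/2.5 = 8.6 to 29.1/2.5 = 11.6 times.

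**Power of one agency-level test.** Noncentral t, 4 degrees of freedom, noncentrality d × √5, critical value 2.776. Power is 13.8% at d = 0.5 SD and 40.1% at d = 1.0 SD.

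**Would adjusting the tests help?** Bonferroni over 15 gives 0.05/15 = 0.0033 per test and a critical value of 6.254. The observed mean change must then exceed 6.254/√5 = 2.80 SD. Power falls to 1.2% at 0.5 SD and 5.1% at 1.0 SD.

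**Would a lead measure alone help?** Only in part. One instrument tested in five agencies still gives 1 − 0.975^5 = 11.9% for a false increase. One overall test brings it to 2.5%, provided the analysis allows for agency. Ignoring clustering, 25 pairs give 67.0% power at 0.5 SD. That figure is optimistic if changes within an agency are alike.

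**The case against.** *It is a pilot.* Considerations and limitations calls Aim 2 foundational pilot research and limits its ambition to "assess potential implementation strategy effects to the use of ISMM within this common service system". No go or no-go decision hangs on a readiness p-value. Interviews and a joint display are planned to interpret agreement and disagreement between data sources. This stands: strict family-wise error control is not required here. But an exploratory aim is better served by an estimate with an interval than by 15 small significance tests, and the joint display can use estimates equally well.

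*The significance level and multiplicity policy may be in a fuller document.* This also stands, and their absence from a condensed article is not the complaint. The testing structure is in the article itself, and a multiplicity adjustment elsewhere could not rescue it, as the 1.2% power shows.

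*The count of 15 is a reading.* The phrase about each agency could describe where the measures are taken, with pooled testing intended. There would then be three tests and at most 1 − 0.975^3 = 7.3% for a false increase. Per-agency testing is the more natural sense, but the wording should be settled.

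*A reader might infer that a false finding of increased readiness is more likely than not.* The documents do not support that. The 54% figure either counts false decreases too or needs one-sided 5% tests, and in both cases it needs independent instruments. The article states neither level nor sidedness. Three scales with one stated purpose, answered by the same people, are unlikely to be independent.

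**Conclusion.** The point holds as a weakness in how the readiness conclusion would be drawn. One directional question is met with about 15 tests of five pairs on three instruments of equal standing, and the article gives no way to combine them.

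With two-sided 5% testing assumed and no true change, the chance of at least one false increase is about 21% to 29% at between-instrument correlations of 0.9 to 0.5. It ranges from 12% to 32% over all correlations from 1 to 0, against 2.5% for a single test. At the same time each test has about 14% power at 0.5 SD. The plan is therefore exposed to a false positive somewhere while being unlikely to detect a moderate change in any one agency.

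The figures rest on the assumed level, sidedness, total scores and independent agencies. Influences shared across agencies would lower the false-increase figures somewhat, and subscale testing would raise them. This is a change that should be made, not a flaw that invalidates the pilot.

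**What to change.** Before data collection, amend the Readiness for change section and the Quantitative analysis plan as follows.

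1. Name one of the three instruments as the lead readiness measure and specify the score. Choose it on measurement grounds, such as reliability, sensitivity to change and fit to the agency setting, and give the reason.
2. Base the Aim 2 readiness conclusion on the pre-post change in that measure over all 25 participants, with a 95% confidence interval that allows for agency. Agency as a fixed effect (25 − 5 = 20 residual degrees of freedom) describes the average change in these five agencies. An analysis of the five agency means (4 degrees of freedom) speaks more to agencies in general, but its interval will be wide. State which is meant.
3. Report the other two instruments, and every per-agency result, as estimates with confidence intervals and without significance claims. Carry them into the joint display.

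No instrument is dropped and data collection is unchanged. The cost is a few sentences, but it is a real change in the unit of analysis. Two instruments lose equal standing, and with only five agencies the interval that allows for clustering will be wider than a naive pooled one.
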